The sample size of 150 mother-infant pairs per maternity is based on a series of power calculations using various prevalence estimates of the prevalence of EBF at 6 months in the control group (15% to 35% for usual care) and a minimum expected effect size of RR = 1.5 for the first objective – comparison of BFHI steps 1-9 to usual care (figure 2.a) and a prevalence of EBF at 6 months in the BFHI steps 1-9 group of 45 to 65% and a minimum expected effect size of RR = 1.3 for the second objective – comparison of the provision of support in the well-child clinics in addition to the implementation of BFHI steps 1-9 in maternities vs. BFHI steps 1-9 in maternities alone (figure 2.b). Assuming two-tailed Person chi-square test with α values of .05, the sample size of 900 mother-infant pairs should provide adequate power to detect a modest difference in the proportion of infants exclusively breastfed at 6 months between BFHI alone and usual care arms or between BFHI steps 1-9 + well-child clinics arm and BFHI steps 1-9 alone.

To determine the number of clusters of size n = 150 that will be needed to achieve an 80% power, we used the formula proposed by Hayes and Bennett (40). Assuming a coefficient of variation of 25% (which is generally considered reasonable), and a 20% prevalence of exclusive breastfeeding in the “usual care” group, we varied various expected prevalence of EBV that could be achieve with the implementation of the Ten Steps. Results are presented in the figure 3 below. Once the prevalence of EBF in the intervention group reaches 40%, the number of clusters needed falls below 4.

**Figure 2.** Power estimate curves for: a- detecting a minimum effect size of RR = 1.5 comparing the prevalence of EBF at 6 months in the BFHI steps 1-9 group to that in the usual care group and b- detecting a minimum effect size of 1.3 comparing prevalence of EBF at 6 months in BFHI steps 1-9 + well-child clinic group to that in BFHI steps 1-9 group for a sample of n = 150 per health facility, n = 300 per randomization group, and n = 900 total for various prevalences of exclusive breastfeeding at 6 months.

Figure 3. Number of clusters of size 150 needed to achieve 80% power for a fixed coefficient of variation of 0.25 by the expected proportion of EBF in the intervention group, assuming a 20% prevalence of EBF in the usual care group.

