Assuming a loss to follow-up rate of 10% over the 6 months - the duration of the follow-up in the study, the effective sample size that will be available for analysis is 135. With this effective sample size, our study will have an 88% power to detect a modest 30% increase in the prevalence of exclusive breastfeeding at 6 months in the intervention group – corresponding to a change as small as an increase from the current proportion of EBF at 6 months of 17% (assuming it stays the same in the usual care group) to 22.5% after implementing BFHI steps 1 through 9.

At the end of the evaluation, the findings of the study will be shared with all facilities that took part in the study and with the community. Facilities in the usual care arm will be encouraged to implement the most successful intervention.

1. **Sustainability and Potential for Scaling-Up**

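### Objective 1 is powered on effects that disagree, two facilities per arm miss 80% power at every effect quoted, and the stated 88% does not reproduce

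*Protocol*

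**What the plan says.** All of this is in the protocol, section B, under Evaluation (the sample-size paragraphs and the captions of Figures 2 and 3), except the allocation, which is under Project Design and Implementation Plan.

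- **Minimum effect.** The plan states "a minimum expected effect size of RR = 1.5 for the first objective", with control prevalence "15% to 35% for usual care". For the well-child clinic comparison it states "a minimum expected effect size of RR = 1.3 for the second objective". This first calculation is at the level of the individual: "Assuming two-tailed Person chi-square test with α values of .05". The text concludes that 900 pairs are enough for a modest difference.
- **Cluster count.** "To determine the number of clusters of size n = 150 that will be needed to achieve an 80% power", the plan uses the Hayes and Bennett formula with a coefficient of variation of 25% and 20% prevalence in usual care. It varies the intervention prevalence and plots the result in Figure 3. The one result given in words is "Once the prevalence of EBF in the intervention group reaches 40%, the number of clusters needed falls below 4". The text does not say whether this is a count per arm or in total.
- **Power after loss.** With 10% loss and an effective size of 135, the plan claims 88% power for "a modest 30% increase in the prevalence of exclusive breastfeeding at 6 months in the intervention group", described as a rise from 17% "to 22.5% after implementing BFHI steps 1 through 9".
- **Allocation.** Six facilities are randomised to three groups. The Figure 2 caption gives 150 pairs per facility and 300 per group, so there are two facilities per arm.

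**The concern.** The 88% sentence concerns the same comparison and outcome as the RR 1.5 minimum, yet it claims high power for an effect below that minimum. The cluster count, the only calculation that respects the randomisation unit, is put into words at a larger effect than either. A reader going through the paragraphs in order can take the favourable count as support for the RR 1.5 minimum, and the 88% as what remains after loss to follow-up.

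If neither holds, the plan overstates what the trial can show. A non-significant result at RR 1.5 could be read as evidence against BFHI steps 1-9 when the design had little chance of detecting that effect. The protocol links national retooling and scale-up to the findings, so this matters for how they are read.

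**Working it through.** **Inputs, all from the protocol.** Two-sided alpha 0.05 and 80% power give (1.960 + 0.842)² = 7.849. Coefficient of variation k = 0.25. Facility size n = 150, or 150 × 0.9 = 135 after loss. Two facilities per arm.

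**Step 1: reproduce the plan's figure.** The Hayes-Bennett formula for unmatched proportions gives facilities per arm as

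c = 1 + 7.849 × {[p0(1−p0) + p1(1−p1)]/n + k²(p0² + p1²)} / (p1−p0)²

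For 20% vs 40% at n = 150:

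- binomial part: (0.16 + 0.24)/150 = 0.00267
- between-facility part: 0.0625 × (0.04 + 0.16) = 0.0125
- c = 1 + 7.849 × 0.01517/0.04 = 3.98

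At 39% the result is 4.19. The count therefore passes below 4 at 40%, as the plan says, and it is a count per arm.

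**Step 2: the same formula at the other quoted effects.** For 20% vs 30% at n = 150, c = 1 + 7.849 × (0.00247 + 0.00813)/0.01, which is 9.31 before rounding. For 17% vs 22.5%, c = 1 + 7.849 × (0.00210 + 0.00497)/0.003025 = 19.35 by the same route.

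**Step 3: power with two per arm.** Rearranging the formula, power = Φ(√[(c−1)(p1−p0)²/V] − 1.96), where V is the term in braces and c = 2. At n = 135 and 20% vs 30%, V = 0.01087, so √(0.01/0.01087) = 0.959 and Φ(−1.00) = 16%. Using c in place of c−1 drops the +1 term.

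| Contrast | RR | Needed per arm, n = 150 | Needed per arm, n = 135 | Power, two per arm, n = 135 (without +1) |
|---|---|---|---|---|
| 20% vs 40% | 2.0 | 3.98 | 4.03 | 36% (62%) |
| 20% vs 30% | 1.5 | 9.31 | 9.53 | 16% (27%) |
| 17% vs 22.5% | 1.32 | 19.35 | 19.96 | 9% (15%) |

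In whole facilities at n = 135 this is 5, 10 and 20 per arm. At RR 1.5 over the plan's control range of 15% to 35%, the need is 10.5 down to 8.3, or 9 to 11 per arm.

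**Step 4: the 88% with clustering ignored.** For the two-tailed chi-square with m = 2 × 135 = 270 per arm,

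power = Φ{[(p1−p0) − 1.96√(2p̄(1−p̄)/m)] / √([p0(1−p0) + p1(1−p1)]/m)}

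For 17% vs 22.5%, p̄ = 0.1975 and the two roots are 0.03426 and 0.03418. Then (0.055 − 0.06716)/0.03418 = −0.356, so power is 36%. It is 39% with 300 per arm and 20% if 135 is read as the arm size. Reaching 88% with 270 per arm would take about 28.3% in the intervention arm (RR 1.66). For 20% vs 30%, individual-level power is 77% with 270 per arm.

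**Step 5: the percentages.** 0.17 × 1.3 = 0.221, and 0.225/0.17 = 1.32.

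**The case against.** Four points on the other side deserve weight.

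1. **The plan names one minimum for objective 1.** A reader might infer that RR 2.0 is another declared minimum. It is not. The 40% value is never called a target; it is where a curve crosses a count. The real conflict between target effects is RR 1.5 against the 30% increase.
2. **Figure 3 may show the 30% point.** A reader might infer that the cluster calculation was done only at the largest effect and that the larger requirement was concealed. The documents do not support that. Intervention prevalence was varied and plotted, and the figure is not available here. What stands is that the text quotes only the 40% point and draws no consequence from smaller effects.
3. **The count might be a total.** The two arms of objective 1 hold four facilities, so a reader could take the count as met. The formula that reproduces the figure counts facilities per arm, so the design has half of what is needed for a doubling at n = 150. It would therefore also be wrong to conclude that the trial is adequately sized for RR 2.0.
4. **22.1% against 22.5% is a small slip.** Agreed: individual-level power is 32% or 36%, and neither is near 88%.

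With 270 per arm and no clustering, about 88% does arise for 45% vs 58.5% (RR 1.3, an objective 2 scenario) and for 25% vs 37.5% (RR 1.5). A figure carried over from another scenario is possible, but the protocol does not say so.

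**Conclusion.** The sample-size text is wrong as written. For one comparison it uses a minimum of RR 1.5, then claims 88% power at RR 1.32, and quotes its cluster count only at RR 2.0. By its own formula, two facilities per arm is half the requirement at RR 2.0, about a fifth at RR 1.5 and about a tenth at 17% vs 22.5% (2/3.98, 2/9.31 and 2/19.35). The 88% is contradicted even before clustering is considered.

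This rests on equal allocation of facilities, the plan's coefficient of variation of 0.25, 135 read as pairs per facility, and the unmatched form of the formula. The plan also says facilities will be matched. The matched form at the same coefficient adds one facility per arm and gives 4.98 at 20% vs 40%, which does not reproduce the plan's figure. The powers for two facilities per arm are normal approximations, so both versions of the +1 term are shown. Neither reaches 80% at any quoted effect.

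**What to change.** - Use one minimum effect for objective 1 in both the power sentence and the sentence that reads Figure 3. RR 1.5 is already named. The Figure 3 curve itself need not change.
- Say that the cluster count is per arm, and quote it at that effect with 135 pairs per facility: 9.5, so 10 per arm, at 20% vs 30% (9 to 11 over control prevalences of 15% to 35%).
- Replace the 88% and the 17% to 22.5% / 30% statement with the power that two facilities per arm give at a coefficient of variation of 0.25: about 16% at 20% vs 30%, or 27% without the +1 term.
- Withdraw the statement that 900 pairs give adequate power for a modest difference.

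The cost is recalculation and rewording, with less favourable stated figures. No added enrolment is required to make the text correct.

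### The claim of adequate power for objective 2 rests on a BFHI-arm prevalence of 45–65% not derived from objective 1, and with two facilities per arm it fails at every stated prevalence

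*Protocol*

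**What the plan says.** All of this is in the Protocol, section B, Evaluation, in the sample-size paragraphs.

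- Objective 1 (BFHI steps 1-9 against usual care) is powered over usual-care prevalences of "15% to 35% for usual care", with "a minimum expected effect size of RR = 1.5 for the first objective".
- Objective 2 (BFHI steps 1-9 plus well-child clinic against BFHI steps 1-9 alone) is powered with "a prevalence of EBF at 6 months in the BFHI steps 1-9 group of 45 to 65" per cent and "a minimum expected effect size of RR = 1.3 for the second objective".
- The basis is individual-level: "Assuming two-tailed Person chi-square test with α values of .05". From this, 900 pairs are judged sufficient for the first comparison "or between BFHI steps 1-9 + well-child clinics arm and BFHI steps 1-9 alone".
- A separate calculation of the number of clusters uses 150 pairs per cluster, a coefficient of variation of 25% and usual care at 20%. It varies only the prevalence reached by BFHI against usual care, and reports that fewer than 4 clusters are needed once that prevalence is 40%.
- After 10% loss, 135 pairs per facility remain. The loss-to-follow-up paragraph gives the current prevalence as 17% and illustrates a small detectable change as a rise "to 22.5% after implementing BFHI steps 1 through 9".

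**The concern.** The BFHI steps 1-9 arm appears in both primary comparisons, as the intervention in objective 1 and the control in objective 2. One planning range should serve both, but the text uses figures that differ widely and does not link them. Power for a fixed risk ratio rises with the control prevalence, so starting at 45% flatters objective 2. The objective 2 judgement also ignores clustering, although the protocol itself adopts a between-facility coefficient of variation and has only two facilities per arm.

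Objective 2 tests the innovation the project proposes, and the section on sustainability ties a significant result to large-scale adoption. If power is far below what is claimed, a non-significant result would say little about whether well-child clinic support works.

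**Working it through.** **Inputs.** Two-sided alpha 0.05; RR 1.3 for objective 2; 300 pairs per arm, or 270 after 10% loss (2 × 135); coefficient of variation k = 0.25; two facilities per arm. All are from the Evaluation section (six facilities in three groups is in Project Design).

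**BFHI-arm prevalence implied by objective 1**
- Full usual-care range: 15% × 1.5 = 22.5%; 35% × 1.5 = 52.5%.
- Usual-care rates used elsewhere: 17% × 1.5 = 25.5%; 20% × 1.5 = 30%.
- To reach 45% at RR 1.5, usual care must be 45/1.5 = 30%. From 17% it takes RR 45/17 = 2.65; from 20%, RR 45/20 = 2.25.
- 65% at RR 1.5 needs usual care of 65/1.5 = 43%, outside the stated range.

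**Power before clustering.** With p1 = 1.3 p0 and p̄ their mean:

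power = Φ{ [ (p1 − p0)√n − 1.96√(2p̄(1 − p̄)) ] / √(p0(1 − p0) + p1(1 − p1)) }

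Example, 30% against 39% with n = 270: (1.479 − 1.318)/0.669 = 0.241, so Φ = 0.595.

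| BFHI arm | Plus well-child clinic | 300 per arm | 270 per arm |
|---|---|---|---|
| 22.5% | 29.25% | 47% | 43% |
| 25.5% | 33.15% | 54% | 50% |
| 30% | 39% | 64% | 60% |
| 40% | 52% | 84% | 80% |
| 45% | 58.5% | 91% | 88% |
| 65% | 84.5% | >99.9% | >99.9% |

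On its own inputs (45–65%, no clustering) the adequacy statement reproduces. The 80% threshold lies at about 38% in the BFHI arm with 300 per arm, or 40% with 270.

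**The plan's cluster formula, reproduced first.** Let V = [p0(1 − p0) + p1(1 − p1)]/m + k²(p0² + p1²). Clusters per arm = 1 + (1.96 + 0.84)² V/(p1 − p0)². For 20% against 40% with m = 150, V = 0.00267 + 0.01250 = 0.01517. With the squared term 7.849, this gives 1 + 7.849 × 0.01517/0.04 = 3.98, matching the reported fewer than 4.

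**Same formula applied to objective 2.** Take m = 135 and two facilities per arm, and let λ = (p1 − p0)/√(V/2). Normal power is Φ(λ − 1.96). The t version uses a noncentral t with 2 + 2 − 2 = 2 degrees of freedom.

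| BFHI arm | V | λ | Normal | t, 2 df |
|---|---|---|---|---|
| 22.5% | 0.01134 | 0.897 | 14% | 9% |
| 30% | 0.01845 | 0.937 | 15% | 9% |
| 45% | 0.03768 | 0.984 | 16% | 9% |
| 65% | 0.07369 | 1.016 | 17% | 10% |

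Prevalence hardly matters here because the between-facility term dominates V. If facilities were infinitely large, λ would be 0.3√2/(0.25√(1 + 1.3²)) = 0.424/0.410 = 1.035 at any prevalence. Normal power would then be Φ(−0.925), about 18%. More mothers per facility cannot repair this. For 80% power the formula asks for 20.5 facilities per arm at 22.5% and 16.2 at 65%, against two.

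**The case against.** **The ranges overlap.** A reader might infer that objective 1 confines the BFHI arm to roughly 22–30%. It does not. The full inputs reach 52.5%, which overlaps 45–65% once usual care is 30% or more. RR 1.5 is called a minimum, so multiplying by it gives a floor rather than an expected value. The protocol's cluster calculation considers 40% in the BFHI arm, where power before clustering is 80–84%. This stands: the mismatch is partial and turns on where usual care falls. What remains is that the 45–65% range is nowhere derived, and that most of it lies above what objective 1 implies.

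**22.5% is not a planned rate.** It illustrates a small detectable change and should not be read as the prevalence the plan expects in the BFHI arm.

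**The origin of the 88%.** The loss-to-follow-up paragraph claims 88% power for a 30% increase. Since 45% against 58.5% with 270 per arm gives 88.3%, a reader might infer that this figure was carried over from objective 2. The documents do not establish that: 25% against 37.5% with 270 per arm gives 88.2%, and Figures 2a and 2b are not available. That the protocol's own example, 17% against 22.5%, gives only about 36% at 270 per arm is a separate error.

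**Clustering.** Facilities are to be matched, which could lower the effective between-facility variation. The protocol gives no smaller value, however, and its reported cluster number reproduces with the unmatched formula at 0.25. It is also fair to say that prevalence ratios with cluster-aware intervals are already planned, so moving to estimation changes little in the analysis.

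**Conclusion.** The adequacy statement for objective 2 is wrong as written. The assumed 45–65% is not reconciled with the objective 1 inputs for the same arm, and at 22.5–30% power before clustering is 43–60% (270 per arm) or 47–64% (300 per arm). Correcting the prevalence alone would not rescue the claim, because clustering is the decisive reason. Under the protocol's own coefficient of variation of 0.25, with two facilities of 135 pairs per arm, power is about 14–17% by the normal approximation and 9–10% with a t reference on 2 df, from 22.5% to 65%. The protocol describes no cluster calculation for this comparison.

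The conclusion rests on RR 1.3, two-sided 5%, the stated coefficient of variation and the unmatched formula that reproduces the protocol's own cluster count. It does not rest on any view of what the BFHI-arm prevalence will turn out to be.

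**What to change.** State one planning range for exclusive breastfeeding at 6 months in the BFHI steps 1-9 arm, consistent with the usual-care rates and RR used for objective 1, and use it for both objectives. Recompute objective 2 power over that range with two facilities per arm, 135 pairs per facility and a coefficient of variation of 0.25, and say whether a normal or t reference is used. Withdraw the statement that 900 pairs give adequate power for objective 2, and present that comparison as estimation, reported as a prevalence ratio with its confidence interval.

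The cost is a recalculation and a few reworded sentences, with no change to recruitment or data collection. The downside is that the stated power becomes much less favourable, which has to be accepted openly.

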Since 2002 and under the leadership of [name], the University of North Carolina at Chapel Hill (UNC) has collaborated with the Congolese Ministry of Health (MoH) and national and local organizations to improve Human Immunodeficiency Virus (HIV) prevention and care through the University Technical Assistance Program (UTAP) with support from various donors. Currently, 44 maternities are supported by our UNC-DRC team serving more than 50,000 pregnant women yearly. These maternities are generally part of a health facility that also hosts a well-child clinic where infants are typically monitored on a monthly basis. As stated above, routine immunization takes place during these monthly visits. To minimize the implementation cost, six of the 44 health facilities with the largest number of deliveries per year will be selected to be part of the study – 3 in urban and 3 in peri-urban areas. Prior to selection, direct observation will be carried out in eligible health facilities to collect information on key characteristics (workload per staff, type of management [government vs private], general infrastructure) that are likely to affect the quality of care. Facilities will be matched for these characteristics prior to randomization. This approach will ensure for example, that health care facilities at the periphery of the city that might have lower patient volumes than facilities in urban areas and serve populations more likely to be socio-economically disadvantaged are included. The selected six facilities will be randomized into 3 groups to receive the following interventions: 1) continuation of current care practices (usual care), 2) implementation of BFHI steps 1-9 in maternities (BFHI steps 1-9), and 3) implementation of BFHI steps 1-9 in maternities and provision of breastfeeding support including culturally appropriate educational messages and metaphors as the ongoing aspect of step 10 in well-child clinic (BFHI steps 1-9 +well-child clinic). The study will be implemented in 2 phases.

Pre-intervention phase

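### The adequate-power statement for 900 pairs ignores facility clustering: objective 2 is never sized for two facilities per arm, and by the protocol's own cluster formula its power is below 80% unless facilities differ very little

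*Protocol*

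**What the plan says.** Under Project Design and Implementation Plan, the protocol randomizes health facilities: "The selected six facilities will be randomized into 3 groups to receive the following interventions". With three groups this gives two facilities per arm. Facilities are to be matched on workload, management type and infrastructure beforehand.

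Under Evaluation, the 150 pairs per maternity come from power calculations for two contrasts:

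- Objective 1, BFHI steps 1-9 against usual care: "a minimum expected effect size of RR = 1.5 for the first objective", with 15-35% exclusively breastfed at 6 months in usual care.
- Objective 2, well-child support added to BFHI steps 1-9: "a minimum expected effect size of RR = 1.3 for the second objective", with "a prevalence of EBF at 6 months in the BFHI steps 1-9 group of 45 to 65" percent.

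The basis is "Assuming two-tailed Person chi-square test with α values of .05", and the conclusion for both contrasts is that "the sample size of 900 mother-infant pairs should provide adequate power to detect a modest difference in the proportion of infants exclusively breastfed". The Figure 2 caption describes the curves as "for a sample of n = 150 per health facility, n = 300 per randomization group, and n = 900 total" and mentions no clustering term.

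The next paragraph brings in the Hayes-Bennett formula for the number of clusters: "Assuming a coefficient of variation of 25% (which is generally considered reasonable"), with 20% prevalence in usual care. It reports that fewer than 4 clusters are needed once the intervention group reaches 40%. No such calculation is given for objective 2.

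**The concern.** Mothers in one facility share staff, training and catchment, so 300 mothers in two facilities carry less information than 300 independent mothers. The protocol recognises this in its cluster paragraph, yet its power conclusion is drawn from the calculation without clustering. The cluster calculation it does give points the other way: it asks for nearly four facilities per arm to detect a doubling, and two are planned.

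Objective 2 is one of two primary objectives and the trial's novel question. The section on sustainability and scaling-up ties large-scale roll-out to a significant result on it. A reader told that power is adequate could take a null result as showing that well-child support adds nothing.

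**Working it through.** **Inputs, all from the protocol.** Two-sided alpha 0.05; target power 80%; m = 150 per facility (135 after 10% loss); two facilities per arm; coefficient of variation k = 0.25; objective 1 at RR 1.5 from 15-35%; objective 2 at RR 1.3 from 45-65%.

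**Formula (Hayes-Bennett, unmatched, per arm).**
S = [p0(1-p0) + p1(1-p1)]/m + k²(p0² + p1²)
c = 1 + (1.96 + 0.84)² × S/(p0-p1)², with the squared term 7.849 before rounding.
Inverted for power at c facilities per arm: Φ(√[(c-1)(p0-p1)²/S] - 1.96).

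**1. Reproducing the plan's figure, 20% against 40%.** S = 0.40/150 + 0.0625 × 0.20 = 0.01517. Then c = 1 + 7.849 × 0.01517/0.04 = 3.98 per arm, which matches the protocol's statement of fewer than 4. With the two facilities per arm actually planned, power for this doubling is Φ(1.624 - 1.96) = 37%.

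**2. Reproducing adequate power without clustering (chi-square, 300 per arm).**
- Objective 2, 45% against 58.5%: (0.135 - 1.96 × 0.0408)/0.0404 = 1.36, so 91%. This rises to about 100% at 65%.
- Objective 1, 15% against 22.5%: (0.075 - 1.96 × 0.0319)/0.0317 = 0.39, so about 65%. At 20% it is 81% and at 35% it is 99%.

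So even without clustering, the low end of the objective 1 range falls short of 80%.

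**3. Objective 2 with k = 0.25, 45% against 58.5%.** S = 0.4903/150 + 0.0625 × 0.5447 = 0.0373, and (0.135)² = 0.018225. Then c = 1 + 7.849 × 0.0373/0.018225 = 17.1 per arm. Power with two is Φ(0.699 - 1.96) = 10.4%.

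Across 45-65%, c is 17.1 falling to 16.2 and power is 10.4-10.7% (10.3-10.7% with m = 135). A cluster-level t-test on the 2 degrees of freedom from two arms of two facilities gives 9.4-9.7%. Dropping the small-sample term altogether gives about 17%.

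**4. Sensitivity of objective 2 (m = 150, Hayes-Bennett).** Each cell gives facilities needed per arm, then power with two per arm.

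| Between-facility variation | 45% | 55% | 65% |
|---|---|---|---|
| k = 0.25 | 17.1; 10% | 16.5; 11% | 16.2; 11% |
| k = 0.10 | 4.8; 30% | 4.2; 35% | 3.8; 38% |
| k = 0.05 | 3.0; 51% | 2.5; 64% | 2.1; 77% |
| k = 0 | 2.4; 66% | 1.9; 85% | 1.5; 98% |
| ICC 0.0156 | 5.7; 25% | 3.9; 38% | 2.6; 59% |

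The last row carries over the intraclass correlation that k = 0.25 implies at 20% prevalence, 0.0625 × 0.20/0.80 = 0.0156. Its design effect is 1 + 149 × 0.0156 = 3.3, which multiplies the binomial part of S in place of the k² term.

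**5. Objective 1 with k = 0.25.** At 15% against 22.5%, S = 0.3019/150 + 0.0625 × 0.0731 = 0.00658, so c = 1 + 7.849 × 0.00658/0.005625 = 10.2 and power with two is 15%. At 35% against 52.5%, c = 8.2 and power is 18%.

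**The case against.** The strongest reply is that 0.25 was never stated for objective 2. The protocol attaches it to the contrast starting from 20% usual-care prevalence. At 84.5% it implies a between-facility standard deviation of 0.25 × 0.845 = 0.21, so one standard deviation above the mean is about 106%, which no proportion can reach. This stands. A reader might infer that the protocol's own assumption gives objective 2 power of 10%, but that figure is an extrapolation. Carrying over the implied intraclass correlation gives 25-59% instead.

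A reader might also infer that the shortfall holds whatever the coefficient. It does not: with no between-facility variation two facilities suffice at 55-65%, and at 45% the need exceeds two (2.4) only because of the formula's added 1. At 0.05, power without that small-sample term would be 80-97%.

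Nor does the protocol print a power of about 90% for objective 2. The text gives no percentage there and Figure 2 is not reproduced, so the 91% is recomputed. The one printed value, 88%, is attached to a rise from 17% to 22.5%, an objective 1 contrast.

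It would also be wrong to say that clustering is ignored throughout, since there is a cluster calculation and the analysis uses GEE. But that calculation covers objective 1 only and asks for more facilities than planned, and GEE does not add power. Matching could lower the effective coefficient, but the protocol puts no figure on the gain and takes no credit for it in the sample size.

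**Conclusion.** The concern holds in this form: adequate power is claimed for both objectives from a calculation that treats mothers as independent, and objective 2 is never sized for the two facilities per arm that the design provides. By the protocol's own formula, objective 2 power stays below 80% across 45-65% at each coefficient examined from 0.05 upward. It is about one in ten at the only coefficient the protocol states. Objective 1 at its stated minimum effect is also far short at that coefficient.

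The direction of the error is firm; its size is not. It rests on the unmatched Hayes-Bennett formula with the added 1, on equal facility sizes, and on a between-facility coefficient for which the protocol gives no local data.

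**What to change.** Replace Figure 2 and the power sentence with cluster-level power for both objectives, at two facilities per arm and 135 analysable infants per facility, for coefficients of 0.05, 0.10 and 0.25 and over the full ranges (15-35% for objective 1, 45-65% for objective 2). In the text:

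- state the formula and, for any t-based figure, the degrees of freedom;
- label 0.25 at 45-65% as an extrapolation from the usual-care contrast;
- note that matching might lower the coefficient by an amount not quantified;
- say that a non-significant objective 2 result is not evidence that well-child support has no effect.

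This costs a recalculation and rewording, with no change to the number of facilities or mothers. The downside is that the stated power becomes much less favourable.

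### The protocol's cluster calculation asks for four facilities per arm (3.98) at 20% vs 40% EBF, but the design has two, so its 80% power target is not met.

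*Protocol*

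**What the plan says.** The Project Design and Implementation Plan section fixes the number of clusters: "The selected six facilities will be randomized into 3 groups to receive the following interventions". The Figure 2 caption in the Evaluation section gives the sizes: "n = 150 per health facility, n = 300 per randomization group, and n = 900 total". That is 300/150 = 2 facilities per arm, and four in each planned two-arm comparison.

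The Evaluation section then sizes the trial in three ways:

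- An individual-level calculation, "Assuming two-tailed Person chi-square test with α values of .05", from which it concludes that 900 pairs give adequate power for a modest difference.
- A cluster calculation with the Hayes and Bennett formula, which is solved for how many clusters of 150 give 80% power. Its inputs are a coefficient of variation of 25% and "a 20% prevalence of exclusive breastfeeding in the “usual care” group". Its result is "Once the prevalence of EBF in the intervention group reaches 40%, the number of clusters needed falls below 4".
- After allowing for 10% loss, so 135 pairs per facility, a claim of 88% power for a rise from 17% to 22.5%.

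**The concern.** The second calculation is the only part of the sample-size justification that carries a between-cluster variance term. (Clustering is also handled elsewhere, through matching of facilities and the GEE analysis.) A reader who sees a requirement below four next to a design with four facilities in each comparison may conclude that clustering was checked and six facilities suffice. If the count is per arm, the check shows the opposite.

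This matters for interpretation. The protocol ties scale-up to showing a significant effect, and a null result from a trial thought to be adequately powered could be taken as evidence that the interventions do not work.

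**Working it through.** **Inputs, all from the protocol.** Two-sided alpha 0.05 (stated for the chi-square calculation and assumed to apply here), power 80%, n = 150 per cluster, k = 0.25, p0 = 0.20, p1 = 0.40. There are two facilities per arm, and 135 analysable pairs per facility after 10% loss.

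**Formula.** For unmatched proportions, the number of clusters per arm is

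c = 1 + (z_α/2 + z_β)² × V / (p0 − p1)², where V = p0(1−p0)/n + p1(1−p1)/n + k²(p0² + p1²) and (1.96 + 0.842)² = 7.849.

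**Step 1: reproduce the stated figure.**

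V = 0.16/150 + 0.24/150 + 0.0625 × (0.04 + 0.16) = 0.002667 + 0.0125 = 0.015167

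c = 1 + 7.849 × 0.015167/0.04 = **3.98**

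At p1 = 39.5% the result is 4.08, so the count drops below 4 between 39.5% and 40%, which agrees with the protocol.

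**Step 2: test the other readings.**

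| Reading | Result at 40% | Fits the sentence? |
|---|---|---|
| Unmatched, per arm | 3.98 | Yes |
| Unmatched, total of two arms | 7.95 | No |
| Matched, per arm (+2 in place of +1) | 4.98 | No |
| Unmatched, per arm, without the +1 | 2.98 (already 3.43 at 38%) | No |

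The stated count is therefore clusters per arm.

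**Step 3: allow for loss to follow-up.** With n = 135, V = 0.4/135 + 0.0125 = 0.015463 and c = 4.03. The count no longer falls below 4 at 40%.

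**Step 4: power with two per arm at 20% vs 40%.**

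- Same formula, solved for power: Φ(√[(c−1)(p0−p1)²/V] − 1.96) = Φ(√(0.04/0.015167) − 1.96) = Φ(1.624 − 1.960) = **36.8%**. At n = 135 it is 36.3%.
- Facility-level t-test: 2(2−1) = 2 df, noncentrality 0.2/√(0.015167/2) = 2.30, power **26.5%**. At n = 135 it is 26.2%.
- Without the +1 term: Φ(√(2 × 0.04/0.015167) − 1.96) = Φ(2.297 − 1.960) = **63%**.
- For comparison, four per arm by the same formula gives 80.3% at n = 150.

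**Step 5: what two per arm could detect.** By the formula, two per arm reach 80% only if EBF rises from 20% to about 78% (c = 1.997), or if k is about 0.11 at 20% vs 40%.

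**Step 6: the protocol's minimum effect for objective 1.** RR 1.5 from 20% is 30%.

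V = 0.16/150 + 0.21/150 + 0.0625 × (0.04 + 0.09) = 0.010592

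c = 1 + 7.849 × 0.010592/0.01 = **9.3 per arm**

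Power with two per arm = Φ(√(0.01/0.010592) − 1.96) = Φ(0.972 − 1.960) = **16%**.

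**Step 7: the 88% statement on the same footing.** For 17% vs 22.5% with n = 135 and k = 0.25:

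V = 0.1411/135 + 0.1744/135 + 0.0625 × (0.0289 + 0.0506) = 0.00731

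Power with two per arm = Φ(√(0.003025/0.00731) − 1.96) = Φ(0.643 − 1.960) = about 9%. The 88% and the cluster calculation cannot both describe this design.

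**The case against.** **A reader might infer that the protocol took a per-arm count for a total and so justified two facilities per arm.** The documents do not support that. No sentence says that two per arm, or four per comparison, is therefore enough. The choice of six facilities is linked to implementation cost. Figure 3 is not shown, and its axis may already say per arm. Likewise, 80% is the target used to solve for the number of clusters; the protocol does not state it as the power of the final design. These points stand. What remains is a stated requirement of four per arm and a design with two.

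**The 37% is not a firm figure.** It inverts a sizing formula at c = 2, where the +1 allowance takes away half the clusters. It also depends on k: the same formula gives about 49% at k = 0.20, 66% at 0.15 and 80% at 0.11. The t-test is not the planned GEE analysis. So a range is right rather than a single number. But at the protocol's k of 0.25, every version stays below 80%, including the most generous at 63%.

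**Facilities are to be matched, and the calculation is unmatched.** True, but the matched form of the formula needs about 5 per arm, so it does not help.

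**The change from 150 to 135 is small.** Agreed. It moves power by half a percentage point and carries no weight by itself.

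**Conclusion.** The point holds. On the protocol's own formula and inputs, 80% power at 20% vs 40% EBF takes four facilities per arm (3.98, or 4.03 after losses), and the design has two. Power for a doubling of EBF is roughly 27–37%, with 63% as an upper bound if the formula's small-sample term is ignored. For the stated minimum effect of RR 1.5 at 20% it is about 16%.

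These figures assume k = 0.25 as the protocol does, two-sided alpha 0.05, and 150 pairs per facility; using 135 lowers them slightly. That the count is per arm is inferred from reproducing it, since the text does not label it. The finding concerns the stated power. It does not show that the trial cannot be run with six facilities.

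**What to change.** In the Evaluation section:

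1. State in the text, and in Figure 3 if it does not already say so, that the count is clusters per arm.
2. Compute it at 135 pairs per facility.
3. Add a sentence such as: with two facilities per arm and a coefficient of variation of 0.25, power at 20% vs 40% EBF is roughly 27–37%, depending on the approximation.
4. Bring the conclusion of adequate power from the chi-square calculation, and the 88% for 17% to 22.5%, into line with this cluster-based figure. If only the cluster sentence is corrected, the protocol would give about 37% for a doubling next to 88% for a 30% relative increase.
5. Describe the trial as estimating effects with wide uncertainty.

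No facilities or participants need be added. The only cost is revised wording and a less favourable stated power.
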